### Exclusion criteria

The diagnosis of chronic illness of the baby, the death of the baby, and the unwillingness of the mother to continue cooperation are the exclusion criteria.

### Data collection method

#### Quality of life questionnaire

The SF-36 Quality of Life Questionnaire is a general questionnaire for assessing the quality of life of individuals; it assesses the quality of life of individuals in 8 domains of physical function, limitations caused by physical problems, social functioning, physical pain, and mental health, limitations caused by mental problems, vitality and general health. The score of each domain is calculated independently and ranges from zero (the worst condition) to 100 (the best condition). Questions of the mentioned dimensions are as follows: physical function (questions 3 to 12); limitation caused by physical problems (13 to 16); social functioning (2, 20 and 32), physical pain (21 and 22), mental health (24 to 28 and 30); limitations caused by mental health problems (17 to 19), vitality (23, 27, 29, 31) and general health (1, 33 to 36). The reliability of this questionnaire has been calculated to be 0.89 and 0.92 by retest and Cronbach's alpha respectively [14].

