#### Quality of life of mothers

The mean score of the Quality of Life of mothers will be measured using a questionnaire SF36 in the pre-test and post-test phases.

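### The printed SF-36 key counts item 27 in both mental health and vitality, giving 37 item assignments for 36 items

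*Protocol article*

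**What the plan says.** The Quality of life questionnaire section of the protocol article says of the SF-36 that "it assesses the quality of life of individuals in 8 domains of physical function" and seven others, and that "The score of each domain is calculated independently and ranges from zero (the worst condition) to 100 (the best condition"). It then lists the items for every domain. The list opens with "physical function (questions 3 to 12"), "limitation caused by physical problems (13 to 16") and "social functioning (2, 20 and 32"), followed by pain with items 21 and 22. It continues "mental health (24 to 28 and 30); limitations caused by mental health problems (17 to 19), vitality (23, 27, 29, 31") and closes with general health, items 1 and 33 to 36.

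Under Outcome measures, the article adds: "The mean score of the Quality of Life of mothers will be measured using a questionnaire SF36", at pre-test and post-test. The Data analysis section counts quality of life among the main research variables, and the Research hypotheses section expects it to rise relative to control.

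No other section repeats the key, corrects it, or says that an item may count in two domains.

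**The concern.** The range given for mental health contains item 27, and the same sentence gives item 27 to vitality. Every other item is placed exactly once, so the key has the form of a one-item-one-domain allocation with a single slip.

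An analyst who codes the domains from this sentence will put one response into two scores. At least one of the two domains then measures something slightly different from what its name says. The two domains also become correlated mechanically through the shared response, and neither the score nor its comparison with other SF-36 data can be fully trusted until the slip is settled. This concerns a main outcome, and the error is easy to carry into syntax because the key looks complete.

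**Working it through.** **Inputs.** All item ranges come from the Quality of life questionnaire section. The total of 36 items follows from the instrument's name and from the highest item number listed.

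**Step 1: expand the key.**

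| Domain | Items as printed | Count |
|---|---|---|
| Physical function | 3 to 12 | 10 |
| Limitation, physical | 13 to 16 | 4 |
| Social functioning | 2, 20, 32 | 3 |
| Pain | 21, 22 | 2 |
| Mental health | 24, 25, 26, 27, 28, 30 | 6 |
| Limitation, mental | 17 to 19 | 3 |
| Vitality | 23, 27, 29, 31 | 4 |
| General health | 1, 33 to 36 | 5 |

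Sum: 10 + 4 + 3 + 2 + 6 + 3 + 4 + 5 = 37 assignments.

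**Step 2: compare with items 1 to 36.** All 36 item numbers occur, so there is no gap. The excess is 37 − 36 = 1, and the only number that occurs twice is 27.

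**Step 3: the two possible repairs.** Each gives 37 − 1 = 36 assignments:

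- Item 27 in vitality only: mental health 24, 25, 26, 28, 30 (5 items); vitality 23, 27, 29, 31 (4 items).
- Item 27 in mental health only: mental health 24 to 28 and 30 (6 items); vitality 23, 29, 31 (3 items).

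**Step 4: size for one mother.** The article gives no formula for turning items into a 0 to 100 score. Assume that a domain score is the plain mean of its items, each on 0 to 100. Let k be the number of items in the domain as printed, x the score on item 27, and m the mean of the other k − 1 items. Including the extra item moves the domain score by

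((k − 1)m + x)/k − m = (x − m)/k.

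- If mental health holds the extra item: k = 6, weight 1/6 = 17%, largest possible shift 100/6 = 16.7 points.
- If vitality holds the extra item: k = 4, weight 1/4 = 25%, largest possible shift 100/4 = 25 points.

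These are ceilings, reached only when item 27 sits at one end of the scale and all the others at the opposite end. The shift is zero when x = m.

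**Step 5: size for the comparison of groups.** The shift is linear. Under the same assumption, the difference between group means therefore moves by (d27 − d)/k, where d27 is the group difference on item 27 and d is the group difference on the mean of the domain's other items. It vanishes if the intervention acts on item 27 as it does on the rest of the domain. The article gives no data from which to estimate it.

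**The case against.** The strongest objection is that this is a short description of an instrument in a journal article, not the scoring syntax. With 35 of 36 items placed correctly as a partition, the likeliest explanation is a range written too broadly or an item listed once too often, and the study team may score from a correct source. This stands as a limit: the scores go wrong only if the printed key is the one used. It does not remove the error, because the article prints a complete key and nothing in it points to another.

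A second objection is that the same key would serve both groups and both time points, so the overlap gives no reason to expect one group to be scored differently from the other. That also stands. What remains is that at least one domain would not measure what it is said to measure.

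Four stronger readings are tempting, but the article does not support them:

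- **That item 27 is a vitality item.** It is named singly under vitality and enters mental health only through a range, where a slip is easier to make. This is suggestive, but the article does not settle which list is right.
- **That the overlap contradicts the scoring statement.** The article says "The score of each domain is calculated independently". The natural meaning is that each domain gets its own score, and two domains that share an item can still be computed separately.
- **That the quality-of-life outcome is undefined because only domain scores exist.** The mean score named under Outcome measures can be read as a group mean of the domain scores. The article uses the same wording for breastfeeding self-efficacy.
- **That item 27 would be counted twice in an overall score.** No section says that the domains will be averaged into a total.

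**Conclusion.** The point holds in a limited form. The printed key makes 37 assignments for 36 items, with item 27 in both mental health and vitality; this is exact and needs no assumption. If the key is applied as printed, at least one of these two domain scores contains a foreign item: one of six in mental health or one of four in vitality. The 17% and 25% weights, and the ceilings of 16.7 and 25 points for a single mother, assume equally weighted items averaged on 0 to 100. Typical shifts would be smaller, and the effect on the group comparison cannot be sized from the article.

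The other six domains, breastfeeding self-efficacy and the growth indices are untouched. So is the sample size, which rests on breastfeeding self-efficacy. It is a small but definite error in the scoring rule of a main outcome and should be corrected.

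**What to change.** Before any questionnaire is scored, check the two lists against the scoring instructions of the SF-36 version in use, and keep item 27 in one domain only, by whichever of the two repairs in step 3 those instructions support. Correct the key in the Quality of life questionnaire section and make the scoring syntax agree with it. A simple safeguard in the syntax is to confirm that the eight item lists together contain each of items 1 to 36 exactly once.

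The cost is one line in the article and a check of one line in the syntax. No data collection changes. If scores have already been computed with the printed key, the affected domain can be recomputed, provided that the item responses were kept.

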#### Breastfeeding self-efficacy scale

The breastfeeding self-efficacy scale is derived from the short form of BSES-SF Dennis. This 14-item scale is designed based on a 5-point Likert scale; so that, I am not sure at all is given score 1, and scores 2 to 5 are given to a bit sure, relatively sure, I am sure, and I am quite sure, respectively. Generally, the range of scores is 14–70, where scores of 14–32 indicate a low level of self-efficacy, 33–51 moderate self-efficacy, and 52–70 high self-efficacy. This scale has been evaluated psychometrically in the study of Araban et al. and its content and form validities have been confirmed; Cronbach's alpha has also been evaluated to be optimal (0.91) [24].

#### Evaluation of the infants' anthropometric indices

The infant's anthropometric indices will be measured using the ratios of infant weight, height, and head circumference recorded on the infant's health card or health record in the pre-test and post-test stages.

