## Research hypotheses

The hypothesis is that after the intervention, the mean scores of infant growth indicators, mothers' breastfeeding self-efficacy, and mothers' quality of life will increase compared to the control group.

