### Inclusion criteria

Inclusion criteria include willingness to participate in the study, primiparous mothers, having an under one-year-old infant, physical health of the child and absence of chronic diseases and chromosomal-genetic defects, no underlying disease, access to mobile phones for connecting to virtual space, ability to use internet and media literacy. Iranian nationality, consent to participate in the study, ability to understand questions or literacy for reading and writing, and not participating in any other clinical trials at the same time.

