### Data analysis

To describe the state of the data, statistics such as the mean and standard deviation of the main research variables (growth rates of infants, breastfeeding self-efficacy, and quality of life) will be determined, and finally, by using SPSS version 22 the mean score of the main variables of the research before and after the intervention will be compared (if the data are normal) with paired t-test and (if the data are not normal) with the non-parametric Wilcoxon test. The randomized trial, will be the statistical analysis "per protocol". 95% confidence interval and P-value < 0.05 will be considered to investigate the effect of the intervention on the mean of the main research variables.

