#### Infants’ growth status

Infant's anthropometric indices (weight-for-age evaluation, height-for-age evaluation, assess weight for height, and assess head circumference for age and body mass index (BMI) for age( will be measured using the ratios of infant weight, height, and head circumference recorded on the infant's health card or health record in the pre-test and post-test stages.

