Generalizing of the results of the study according to the cultural, social and nutritional differences in different societies will be one of the challenges of this study. The non-generalization of the study results to mothers of premature infants and mothers with twin infants or mothers and infants with special conditions will be a restriction. The limitation of the statistical population, the busyness of mothers, neglect of educational packages, receiving information by mothers from other members of the health team, and sharing information and experiences of mothers outside the group and without the supervision of researchers will be other restrictions of this study. This study may not be generalizable because people without telephones will be excluded from participating in the intervention, and this is another limitation of this study.

However, According to the investigations, the current educational package not only combines virtual education and peer experiences in strengthening the education of mothers, but also it can improve mothers' physical and mental health and reduce medical costs by using telephone follow-up in supporting the mothers of infants. Additionally, the strategy used in this protocol can be used for education and support in pre-pregnancy, pregnancy and childbirth care. The strategies of this program could be important and cost-effective, and therefore we hope that the success of such a program is a step forward in improving maternal and infant health status.

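### The scale of the infant growth outcome is not fixed, and the only test named for it is a before-after test that does not address the between-arm hypothesis and may pick up normal growth

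*Protocol article*

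**What the plan says.** The protocol article describes the growth outcome in four places, and they do not agree.

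- **Evaluation of the infants' anthropometric indices:** the indices "will be measured using the ratios of infant weight, height, and head circumference recorded on the" infant's health card or health record, at the pre-test and post-test stages. What the ratios are taken against is not said.
- **Outcome measures, Infants' growth status:** the same ratio wording, but the indices are listed as "weight-for-age evaluation, height-for-age evaluation, assess weight for height, and assess head circumference for age and body mass index (BMI) for age". No z-score or percentile scale is mentioned.
- **Data analysis:** growth is one of the "main research variables (growth rates of infants, breastfeeding self-efficacy, and quality of life"). The tests named are a paired t-test on values before and after the intervention or, if the data are not normal, a Wilcoxon test in the same role. No between-group test is named.
- **Research hypotheses:** "the mean scores of infant growth indicators, mothers' breastfeeding self-efficacy, and mothers' quality of life will increase compared to the control group".

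On the population, Inclusion criteria ask for "having an under one-year-old infant, physical health of the child and absence of chronic diseases". Neither these nor Exclusion criteria mention gestational age or multiple birth. The Discussion nevertheless lists as a restriction "The non-generalization of the study results to mothers of premature infants and mothers with twin infants".

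Phase II states that allocation to the two groups is random and that controls are evaluated in the same way as the experimental group.

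**The concern.** A ratio of body measurements, a growth rate and a for-age index are three different quantities. The first two change as an infant gets older, whatever the programme does. A for-age score on a suitable standard largely removes that change. The article does not commit to one of them.

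This matters because of the test. A paired before-after test asks whether the mean has moved within a group. Every infant grows between the two measurements, so on an unstandardised scale the answer is almost certainly yes, in the control group as well. The hypothesis asks something else: whether the intervention arm moved more than the control arm. A team that follows Data analysis as written could report normal growth as an effect and never carry out the comparison that the randomisation was set up to provide.

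There is also a problem of direction. The hypothesis treats an increase in every growth indicator as the desired result. For BMI-for-age and weight-for-height, a higher value is not a benefit for every infant.

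**Working it through.** **1. The plan's own figure.** Study sample gives SDs 4.22 and 4.88, a difference of 2.5 points, α = 0.05, power 0.80, 10% drop-out and 57 per group. With the usual formula for two means,

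n = (1.960 + 0.842)² × (4.22² + 4.88²) / 2.5² = 52.27,

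and 52.27 × 1.1 = 57.5, so the stated 57 is reproduced to within rounding. It concerns breastfeeding self-efficacy. The article gives no figure for growth. Its use here is the number of completers: 57 × 0.9 = 51.3, so 51 per arm.

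**2. The paired test in one arm when the programme has no effect.** Let m be the mean change from normal growth, or from drift of the score, divided by the SD of the change. The documents give no value for m, so a range is shown. The paired t statistic has 50 degrees of freedom and noncentrality m√51 = 7.14m, with a two-sided 5% limit.

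| m (assumed) | Probability of P < 0.05 with no effect |
|---|---|
| 0 (standardised score, no drift) | 0.05 |
| 0.1 | 0.11 |
| 0.2 | 0.29 |
| 0.3 | 0.56 |
| 0.5 | 0.94 |
| 1 or more | 1.00 |

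The nominal level holds only in the first row. Even a small drift against the growth standard (m = 0.1 or 0.2) raises the rate to 0.11 or 0.29.

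**3. The between-arm test under the same conditions.** The simulation used 20,000 runs, 51 infants per arm, entry ages uniform over 0 to 12 months and no effect. Change was 2m(1 − age/12) plus noise with SD 1, so growth slows with age and its mean is m. Here m is in units of the within-age SD.

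| m | Paired test, one arm | Between-arm t-test on change |
|---|---|---|
| 0.5 | 0.922 | 0.049 |
| 1 | 1.000 | 0.049 |
| 2 | 1.000 | 0.051 |

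The between-arm comparison keeps its 5% level although the ages are widely spread.

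**4. What the age spread costs.** In this model the variance of change due to age is (2m)²/12 = m²/3, against a within-age variance of 1. The share due to age is therefore 0.083/1.083 = 8% at m = 0.5, 0.333/1.333 = 25% at m = 1 and 1.333/2.333 = 57% at m = 2. That is a loss of precision, which standardisation and adjustment for age would largely recover. It is not bias.

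**5. Eligibility set beside the Discussion.** Requiring primiparous mothers does not rule out a first twin birth, and requiring a physically healthy child does not rule out a healthy infant born preterm. So the criteria admit both groups, while the Discussion writes as if they were outside the study.

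**The case against.** The strongest reply is that Infants' growth status does list for-age indices, and that *ratios* may simply be loose English for them. If the analysed values are standardised scores, normal growth and age are largely removed, and the paired test rejects at about 0.05 when there is no drift. This stands. It means that the high rejection rates hold only under the less favourable reading, and that a calculation on kilograms of weight gain would test an outcome the article does not list. It does not rescue the plan: the text leaves both readings open, and under either one the paired test does not compare the arms.

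A second reply is that a condensed article leaves detail to the full protocol or analysis plan. That is fair for the choice of growth reference and for a window around measurement dates. It does not cover a test that the article states and that does not match its own hypothesis.

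A reader might infer four stronger things, which the documents do not support:

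- *The hypothesis counts any before-after rise as success.* It does not; the increase is relative to control. The before-after element comes from Data analysis.
- *The wide age range biases the comparison.* Allocation is random, so age is balanced in expectation, and the simulated error rate stays near 0.05.
- *Card measurements will be taken away from the test dates.* The article places them at the pre-test and post-test stages; nothing says otherwise.
- *A mother of twins contributes two correlated records.* The article speaks of mother-infant pairs, which suggests one infant per mother.

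**Conclusion.** The point holds in a limited form. The growth variable is described in incompatible terms, so it is not fixed whether it is age-standardised. The only test named does not address the stated between-arm hypothesis. Normal growth *may* therefore be read as an effect; it would not be if the indices were age-standardised and the arms compared.

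The size depends on assumed values of m and on 51 completers per arm. With no effect, the paired test is significant with probability 0.94 at a mean change of 0.5 SD and 1.00 from 1 SD upwards, against 0.05 for a standardised score without drift. A between-arm test stays at about 0.05. Growth does not drive the sample size, so that figure is untouched.

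The mismatch between the eligibility criteria and the Discussion is real but secondary. It needs only to be reconciled.

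**What to change.** - In Evaluation of the infants' anthropometric indices, Infants' growth status and Data analysis, replace the ratio and growth-rate wording with age- and sex-specific z-scores, computed from the infant's exact age on the date of each recorded measurement. Weight-for-height is standardised on height and sex instead of age. The growth reference can be named in the full protocol or analysis plan.
- For growth, replace the before-after paired or Wilcoxon test with a between-arm comparison of the post-test z-score, adjusted for baseline z-score and age, reported with its 95% confidence interval. Within-arm changes can remain as description.
- State the growth hypothesis as two-sided, and make no claim of an increase for BMI-for-age and weight-for-height.
- Reconcile Inclusion criteria and Exclusion criteria with the Discussion on preterm and twin infants. Either the criteria or the limitation can be reworded, provided that they describe the same population.

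The cost is a little extra analysis work and the recording of measurement dates. The sample size does not change.

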### Data analysis

To describe the state of the data, statistics such as the mean and standard deviation of the main research variables (growth rates of infants, breastfeeding self-efficacy, and quality of life) will be determined, and finally, by using SPSS version 22 the mean score of the main variables of the research before and after the intervention will be compared (if the data are normal) with paired t-test and (if the data are not normal) with the non-parametric Wilcoxon test. The randomized trial, will be the statistical analysis "per protocol". 95% confidence interval and P-value < 0.05 will be considered to investigate the effect of the intervention on the mean of the main research variables.

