## Phase II: implementation of educational intervention

In this step a randomized controlled clinical trial will be design to assess the efficacy of the prepared protocol. Participants will randomly be allocated into two groups. In the experimental group we will implement our designed protocol, and the control group will not receive any intervention, but they are evaluated as the same as the experimental group. For ethical issues all educational material will offer at the end of the study (Fig. 1).

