### Study sample

This interventional randomized study will be conducted on mothers of infants who have been receiving maternity care at health centers in Yazd, Iran. According to the study of Araban et al. [24] and considering the level of significance (α = 0.05) and test power (β = 0.8) as well as the standard deviation of breastfeeding self-efficacy score which is 4.22 and 4.88 in case and control groups respectively, and in order to achieve a significant difference of at least 2.5 points in the mean score of breastfeeding self-efficacy in the intervention and control groups, and taking into account 10% of probable drop, the sample size is considered to be 57 subjects in each group using the following formula.$$n = \frac{{\left( {Z_{{1 - \frac{\alpha }{2}}} + Z_{1 - \beta } \left( {\sigma_{1}^{2} + \sigma_{2}^{2} } \right)} \right)}}{{d^{2} }}$$

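### The only inferential test named is a before-after paired test, so the plan contains no test of its between-group hypothesis and makes no inferential use of the randomised control arm

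*Protocol article*

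**What the plan says.** Four places in the protocol article bear on this.

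- **Research hypotheses:** after the intervention, infant growth, "mothers' breastfeeding self-efficacy, and mothers' quality of life will increase compared to the control group". The contrast is between groups.
- **Phase II:** "Participants will randomly be allocated into two groups", and the controls are assessed in the same way as the experimental group.
- **Study sample:** the trial is sized to detect a "significant difference of at least 2.5 points in the mean score of breastfeeding self-efficacy in the intervention and control groups", with a separate SD for each group (4.22 and 4.88), giving 57 per group after allowing for 10% loss.
- **Data analysis:** after descriptive statistics, the means of the "main variables of the research before and after the intervention will be compared (if the data are normal) with paired t-test" or, "if the data are not normal) with the non-parametric Wilcoxon test". The section closes with a general criterion: "95% confidence interval and P-value < 0.05 will be considered to investigate the effect of the intervention on the mean of the main research variables".

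The article names no independent-samples t-test, rank-sum test, comparison of change scores, ANCOVA or group-by-time model.

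**The concern.** A paired test asks whether the mean in one set of people changed over time. It does not ask whether that change was larger than in the control group. A significant change in the intervention arm does not answer the trial's question. Nor does finding a significant change in one arm and a non-significant change in the other, because the difference between two p-values is not a test of the difference between two effects.

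What is at stake is the value of the randomisation. Mothers' confidence and quality of life may shift over the two to three months of the programme simply with experience and time since birth. If so, a before-after test attributes that shift to the programme, and its error rate with respect to the actual hypothesis is not controlled. The growth outcomes face the same risk to the extent that they are analysed as raw weight, height or head circumference, all of which rise with age in any infant.

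**Working it through.** **1. Which comparison does the sample size presuppose?**

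Inputs from Study sample: SDs 4.22 and 4.88, difference 2.5, α = 0.05 (two-sided, since the formula uses Z at 1 − α/2), power 0.80, 10% loss.

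- Sum of variances: 4.22² + 4.88² = 17.81 + 23.81 = 41.62. The root mean square SD is √(41.62/2) = 4.56.
- Two independent means: n = (1.96 + 0.8416)² × 41.62 / 2.5² = 7.849 × 41.62 / 6.25 = 52.3 per group.
- With 10% added: 52.3 × 1.1 = 57.5, consistent with the stated 57. (52.3/0.9 = 58.1 is also close.)

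A paired test of a 2.5-point change would use the SD of change, 4.56 × √(2(1 − r)). It would need 37, 27 or 16 pairs for an assumed pre-post correlation r of 0.3, 0.5 or 0.7. So the stated 57 comes from a comparison of two independent groups, which the Data analysis section does not contain.

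**2. What does the paired test do when the programme has no effect?**

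Assumptions not in the document: both arms change by the same amount, and r is 0.3 to 0.7. Completers: 57 × 0.9 ≈ 51 per arm. SD 4.56 as above.

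- SD of change: 5.40, 4.56, 3.53 for r = 0.3, 0.5, 0.7.
- Noncentrality: common change × √51 / SD of change. For 1 point at r = 0.5 this is 7.14/4.56 = 1.57.
- Probability of a significant increase in the intervention arm (noncentral t, 50 degrees of freedom, two-sided 5% test):

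| Common rise (points) | r = 0.3 | r = 0.5 | r = 0.7 |
|---|---|---|---|
| 0 | 2.5% | 2.5% | 2.5% |
| 0.5 | 10% | 12% | 17% |
| 1 | 25% | 34% | 51% |
| 1.5 | 50% | 63% | 84% |
| 2 | 74% | 87% | 98% |

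**3. Does running the paired test in each arm and comparing verdicts help?**

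With no true effect, the arms are independent and each shows a significant increase with probability p. The chance that the intervention arm does and the control arm does not is p(1 − p). At r = 0.5:

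- 1 point: 0.336 × 0.664 = 22%
- 1.5 points: 0.634 × 0.366 = 23%
- 2 points: 0.867 × 0.133 = 12%

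Across r = 0.3 to 0.7 and rises of 1 to 2 points, this ranges from about 2% (r = 0.7, 2 points, where both arms are nearly always significant) to 25%.

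**4. What would a between-group analysis deliver with the same participants?**

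For a 2.5-point difference with 51 per arm, normal approximation:

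- Unadjusted: SE = √(41.62/51) = 0.903; 2.5/0.903 = 2.77; power 79%.
- Adjusted for the pre-test score: SE = √(41.62 × (1 − r²)/51) = 0.862, 0.782, 0.645; power 83%, 89%, 97% for r = 0.3, 0.5, 0.7.

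Using the t distribution lowers these by about one percentage point at most.

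**The case against.** The strongest reply is that this is a condensed article. It states a contrast with control, describes a pretest-posttest design for both groups, and sets a confidence level and p-value threshold for the effect of the intervention, so a between-arm test may be intended and set out elsewhere. That limits the wording: what can be said is that no between-arm comparison is specified, not that the authors have decided against one. It does not remove the point. The article does not defer the test; it names one, and that test cannot address the hypothesis. The closing criterion names no contrast with control. The Wilcoxon test appears as the counterpart of the paired t-test in the same before-after sentence, so it reads as the signed-rank test; were it the rank-sum test, the normal-data branch would still lack a between-arm comparison.

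Several narrower objections stand:

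- The size of any natural change is unknown. Infants may enter at any age under one year, so many mothers may be well past the early post-partum period. With no common change, the paired test in the intervention arm keeps its nominal rate.
- Under Outcome measures, growth is largely expressed as age- or height-referenced indices, which need not rise with age. The description under Data collection method is looser, so the risk from raw measurements is possible rather than certain.
- Regression to the mean is not a good argument here, because mothers and infants are not selected on an extreme baseline score.
- Comparing verdicts across arms is a rule the document does not state. It is shown only because it is the usual way paired tests in two arms get read.
- Choosing between the t-test and Wilcoxon by a normality check is a minor matter beside the missing comparison.

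**Conclusion.** The concern holds. The stated analysis is within-group, while the hypothesis, the randomisation and the sample size are between-group, and the 57 per group is consistent only with a comparison of two independent groups. This conclusion follows from the text and needs no assumption.

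The size of the error does rest on assumptions: no true effect, SD 4.56, 51 completers per arm, correlation 0.3 to 0.7, and a rise common to both arms. Under these, a rise of 1 to 2 points gives a 25% to 98% chance that the intervention arm's paired test shows a significant increase. This must be corrected before analysis, because the procedure as written cannot test the trial's own hypothesis.

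**What to change.** Replace the paired t-test/Wilcoxon sentence with wording such as: *For each outcome, the intervention effect is the difference between the intervention and control groups at post-test, estimated by ANCOVA of the post-test value on group and the pre-test value, with a 95% confidence interval and two-sided p-value. Within-group changes are reported descriptively only.*

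Baseline adjustment is the recommended form because of the precision it brings; an unadjusted comparison of the two groups would also repair the mismatch. Infant age and health centre are sensible further covariates but optional. If non-normality is a worry, specify robust or bootstrap standard errors in advance rather than switching tests after a normality check.

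The cost is a change of wording. Both arms already complete the questionnaires before and after the intervention, anthropometry is taken from the records at both stages, the model runs in the named SPSS software, and the sample size need not rise.
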